### 3.12 What is the planned recruitment rate?

What evidence is there that it is achievable? We will recruit the 148 infants for the trial over the first 3 of 6 grant years (4 to 5 infants/month) as well as the reference group (n=74); also see **Table 2**. We will ensure the reference group is frequency matched by season to reflect the trial's proportion of white:non-white infants. The recruitment rates are realistic since in the past we have recruited 227 infants over 3.5 years for 3 different studies [3, 15, 16] related to vitamin D out of one hospital and 5 pediatric clinics. Assuming ~24% of infants have low vitamin D status, the estimate for screening is at least 592 infants. To account for those not wishing to participate we will screen 2000 neonates yearly. Given the recruiting hospitals, St. Justine Hospital which specialises in maternal-child health and where co-applicant [name] is appointed and actively recruits for trials [17]; McGill University Hospital Centre; and Lakeshore General Hospital where [name] has recruited, we do not anticipate having difficulty meeting these numbers.

### 3.13 Are there likely to be any problems with compliance?

Based on our studies [3, 15, 16], compliance for vitamin D supplementation is very high (86-90%) in breast fed and weaned infants (84%). We will educate the parents on the importance of giving the supplement at all times regardless of intake of vitamin D from other sources (mother's milk, weaning milks, egg yolk etc). Compliance will be evaluated by parent self-report of dosages given as ascertained at each visit, by pre and post-weighing of bottles of supplement used and our biological response data (serum 25(OH)D).

### 3.14 What is the likely rate of loss to follow up?

We anticipate a 5-10% loss to follow-up. Previously we had <4% loss to follow-up at 3 mo [15]. In our dose-response study [3] a higher loss to follow-up of 12% was ascribed to additional blood sampling for safety assessments; which is not as likely in the present study design where we will use lower dosages (i.e. 1000 IU/d vs 1600 IU/d). We published our attrition data which were initially higher when the safety issues were being resolved and learned that healthy infants have higher ionized calcium than previously thought [6].

### 3.15 How many centers will be involved?

One research centre with recruitment from 1 hospital that we work with; recruitment site will be documented for each infant and considered in the analyses.

### 3.16 What is the proposed type of analyses?

Intent-to-treat analyses. All data entry will be audited and baseline characteristics expressed as mean (SD) or median (IQR) depending on normality for continuous data or as proportions for ordinal data (e.g. white non-white, sex). Continuous data for primary outcome measurements will be expressed as mean (95% CI) or proportion (95%CI). All data analysis will be conducted using SAS (version 9.3, SAS Inst. and SAS University Edition). Continuous data for the primary outcome will be examined using mixed model ANOVA accounting for fixed effects (sex,

dosage, time, dosage\*time) and random effects (e.g. infant ID.) with post-hoc testing as applicable (i.e. 2 treatment groups and 1 reference group over 4 time-points) using Tukey-Kramer correction and significant differences accepted at  $p < 0.05$ . The mixed model ANOVA does not require that data be parametric nor of homogeneous variance. Data will be tested using Kolmogorov-Smirnov, Anderson-Darling, or a Shapiro-Wilk tests for normality and where necessary transformed (e.g. log value etc.) to meet the assumptions of the post-hoc tests. The mixed model uses all available data, missing data does not result in omission of an infant's existing data. If more than 5% of data is missing, imputation approaches will be considered. Compliance (unused product and surveyed data) will be compared between groups. For the secondary objectives, a MIXED model will be used for continuous data. The proportion of those achieving the 50 and 75 nmol/L targets will be expressed as a proportion (95% CI) and differences among groups tested using Chi-square analyses or other similar tests based on numbers in each cell or logistic regression. We are experienced in all of these tests [3, 15]. The healthy reference group will be statistically analyzed to form reference curves (e.g., lean mass) using LMS methods [18].

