## 2. Trial objectives

Primary Trial Objective: To test whether rapid correction of vitamin D status early in the neonatal period results in greater lean mass by 3 mo of age and sustained to 3 y. It is hypothesized that neonates with low vitamin D status and provided a vitamin D supplement of 400 IU/d will have lower accretion of lean mass by 3 mo of age and thereafter to 3 y compared to infants given 1000 IU/d.

Secondary Trial Objectives are designed *a priori* to test:

1) Whether correction of low vitamin D status early in infancy using 1000 IU/d of vitamin D normalizes body composition (lean, fat, bone mass) across infancy and to 3 y of age;

Tertiary Objective: outside of the trial, establish a healthy reference group with good neonatal vitamin D stores ( $>50$  nmol/L 25(OH)D) and given the AI of 400 IU vitamin D/d with all of the same measurements as the trial since these are not all available (e.g. IGF-1, IGFBP3 using same assays). The reference group will be frequency matched to trial infants based on skin color of the infants and season.

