### 3.11 What is the proposed sample size and what is the justification?

The minimum sample size (n=66) is based on the primary objective, lean mass in g at 3 mo of age and an effect size of 9% (400 g), SD of 670 g, an allocation ratio of 1:1, power of 80 and alpha of 0.01. Accounting for possible dropouts ( $\leq 10\%$ ) or missing data (1% due to movement artifact) we will study 74 infants/group. The attrition is based on 3 similar studies with an average attrition of 9% [3, 15, 16]. We have used a more stringent estimate based on an alpha of

1% to enable multiple comparisons over time and in the event of greater variability in lean mass. We believe the estimated effect size is clinically meaningful since infants in the preliminary healthy status group treated with 400 IU/d increased lean mass between 1 mo and 3 mo by 670 g and the  $\Delta$  400 g anticipated between our trial groups by 3 mo represents 60% of that normal change which would be enough to reset growth for a leaner body phenotype.

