| Length (height)                               |           | x        | x       | x       | x        | x             |
| Head Circumference                            |           | x        | x       | x       | x        | x             |
| Body composition and bone by DXA              |           | x        | x       | x       | x        | x             |
| Surveyed Information                   |           |          |         |         |          |               |
| Obstetrical record                            | x (chart) |          |         |         |          |               |
| Demographic surveys                           | x         | x        |         |         |          |               |
| Adverse events/any illnesses                  |           | x        | x       | x       | x        | x             |
| Dietary/supplement intake & compliance        |           | x        | x       | x       | x        | x             |
| Sun exposure/skin pigmentation                |           | x        | x       | x       | x        | x             |
| Activity (HAES)                               |           |          |         |         |          | x             |

Abbreviations: DXA: dual-energy x-ray absorptiometry; HAES: habitual activity estimation scale;  
IGF-1: insulin like growth factor-1; IGFBP3: insulin like growth factor binding protein 3; LC-MS/MS:  
liquid chromatography tandem mass spectroscopy.

462  
463  
464  
465  
466  
467  
468  
469  
470  
471  
472  
473  
474  
475  
476  
477

Table 2. Study time-lines (6 year grant October 1, 2015 to September 30, 2021)

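### The primary mixed model leaves the 3-month comparison of lean mass unadjusted for the 1-week baseline scan, and so gives up precision that the trial's own data could supply

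*Protocol*

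**What the plan says.** Protocol section 3.16 sets the primary model: "Continuous data for the primary outcome will be examined using mixed model ANOVA accounting for fixed effects" listed as sex, dosage, time and dosage by time, with infant as a random effect. Post-hoc tests cover two treatment groups and one reference group at four time-points. Baseline lean mass is not among the covariates, and no common baseline mean is imposed.

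Section 3.7 lists the visits of the treatment period as 1 week, 3, 6 and 12 months. The section on frequency of analyses places the first primary analysis after the 12-month visits. The four time-points must therefore include the 1-week visit. Table 1 schedules "Body composition and bone by DXA" at baseline and at every later visit, and section 3.4 places allocation after the baseline assessments.

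The hypothesis in section 2 is that infants on the lower dose "will have lower accretion of lean mass by 3 mo of age and thereafter to 3 y compared to infants given 1000 IU/d". Section 3.11 rests the sample size on "lean mass in g at 3 mo of age and an effect size of 9% (400 g), SD of 670 g, an allocation ratio of" (the ratio stated is one to one, so the arms are equal in size). The error rates chosen there are "power of 80 and alpha of 0.01". Stratification (section 3.3) is on skin color only, and the one covariate provision in the subgroup section is for sex.

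**The concern.** A pre-treatment measurement of the outcome usually predicts the later value and so can sharpen the comparison. A model in which every group-by-visit mean is free does not use it for the attained-mass contrast at a later visit. With complete data, that contrast is simply the difference between the two arms' means at 3 months. The baseline scan is paid for and performed but adds nothing to the comparison on which the trial was sized, and a chance baseline difference between arms passes into the 3-month estimate uncorrected. The protocol lists the model terms and the number of time-points explicitly, so this concerns what it states rather than a detail it leaves open.

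**Working it through.** **Inputs.** From section 3.11: difference 400 g, SD 670 g, 1:1 allocation, 80% power, alpha 0.01, 66 per group, 74 after attrition. Sidedness is not stated; two-sided reproduces the figure. Assumed, because the protocol does not give it: the correlation r between 1-week and 3-month lean mass, after accounting for sex, taken as 0.3 to 0.5. The SD of 670 g is treated as the SD within sex.

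**1. The plan's own figure.** n = 2 × 670² × (2.576 + 0.842)² / 400² ≈ 65.5, so 66 per group. Normal-approximation power at 66 is 80.3%. With 10% attrition, 66 / 0.90 = 73.3, so 74. Both stated figures reproduce. The calculation is an unadjusted two-sample comparison at 3 months.

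**2. The model as written.** With a free mean for each group at each visit and complete data, the standard error of the 3-month difference is 670 × √(2/66) = 116.6 g. Generalised least squares on four visits (equal SDs and equal correlations) returned 116.6 g for r = 0.3, 0.5 and 0.7 alike, so the baseline visit contributes nothing to this contrast.

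**3. With baseline adjustment.** The standard error becomes 670 × √(1 − r²) × √(2/66). Generalised least squares with the two arms constrained to a common baseline mean gives the same values. Power is Φ(400/SE − 2.576).

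| r (assumed) | 1 − r² | SE, g | Power, n = 66, two-sided 0.01 | n per group for 80% |
|---|---|---|---|---|
| 0 | 1.00 | 116.6 | 80.3% | 66 |
| 0.3 | 0.91 | 111.3 | 84.6% | 60 |
| 0.5 | 0.75 | 101.0 | 91.7% | 50 |

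**4. The change-from-baseline contrast.** The dosage-by-time term does carry differential change. Assuming the same SD of 670 g at baseline, the 3-month change contrast has a standard error of 670 × √(2(1 − r)) × √(2/66):
- r = 0.3: 138.0 g, power 62.7%
- r = 0.5: 116.6 g, power 80.3%

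This contrast uses baseline, but less efficiently than adjustment (84.6% and 91.7%).

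**5. Chance imbalance.** A baseline difference of one standard error moves the expected unadjusted 3-month difference by r × 116.6 g, which is 35 g at r = 0.3 and 58 g at r = 0.5. The 116.6 g standard error already allows for this.

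**6. The dosage main effect, if it were used.** Suppose the effect were a constant 400 g at 3, 6 and 12 months. Averaged over four visits that include baseline, it would appear as (0 + 400 + 400 + 400) / 4 = 300 g.

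These powers use the planning alpha of 0.01. Section 3.16 instead describes post-hoc tests "using Tukey-Kramer correction and significant differences accepted at" the 0.05 level. A different critical value moves every power figure but leaves the standard errors in step 3 unchanged.

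**The case against.** The strongest reply is that the stated model is valid. Randomisation makes the comparison unbiased on average, chance imbalance is already in the standard error, and the sample size never relied on baseline adjustment. That stands. A reader might infer that the trial is underpowered or the comparison biased, but section 3.11 gives no support for either: the planned 80% is met on its own terms.

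A reader might also infer that the model misses the accretion hypothesis. It does not. With baseline among the visits, dosage by time tests whether change differs between arms. What remains is that this route is less efficient than adjustment.

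A third tempting reading is that the primary test is diluted towards no difference. Nothing in the protocol names the dosage main effect as the primary test, and section 3.11 points to 3 months. The 300 g figure also needs a constant effect at 3, 6 and 12 months, whereas the protocol gives 400 g at 3 months only. The dilution is therefore conditional.

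Three practical objections also stand:
- The gain depends on a correlation that the documents do not report. Because sex is already in the model, the relevant value is the one left after sex.
- Section 3.11 expects about 1% of data to be missing through movement artifact. A plain baseline covariate would drop an infant without a usable baseline scan.
- The reference group is not randomised and is selected on vitamin D status and maternal weight criteria. Adjusting it for 1-week lean mass would change what the comparison with it means.

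The handling of baseline could be refined in a statistical analysis plan. But section 3.16 already lists the terms, so the change is to stated text.

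**Conclusion.** The point holds as one of forgone precision. As written, the primary model gives a 3-month comparison of the randomised arms that takes nothing from the baseline scan. With an assumed correlation of 0.3 to 0.5 after sex, adjustment would cut its standard error from 116.6 g to 111–101 g and lift power from about 80% to about 85–92%, at 66 per arm and two-sided alpha 0.01. At a correlation near zero there would be no gain. That the four time-points include baseline is inferred from the visit schedule and the timing of the 12-month analysis, and it is the only count that fits. The sample size needs no correction on this ground. It is a worthwhile change to the model, not a flaw that invalidates it.

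**What to change.** In section 3.16, for the primary comparison of the two randomised arms, keep 1-week lean mass as a response but constrain the two arms to a common baseline mean. This retains infants without a usable baseline scan. An alternative is to take 3, 6 and 12 months as outcome visits, with 1-week lean mass and its interaction with visit as covariates, and to state how infants with a missing baseline are kept.

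Leave the reference group out of the constraint or adjustment, and describe the comparison with it separately. State that the treatment effect is read from the 3-month dosage contrast and not from the dosage main effect.

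No new data, visits or participants are needed, because the scan is already scheduled. The cost is revised model wording, made before any unblinded analysis, and a separate specification for the reference-group comparison.

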### 3.8 Primary and secondary outcomes:

Primary outcome: lean mass during the trial; with follow-up thereafter to 3 y. Secondary outcomes: body composition including bone mass and BMI z-scores, tissue accretion rates across the study period and follow-up; vitamin D status and mechanistic explanations (IGF-1).

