### 3.17 What is the proposed frequency of analyses?

For the primary outcome, one analysis will be conducted on blinded groups after all infants have completed 12 mo of study and a second analysis again at 3 y. We wish to keep all of the staff blinded across the entire study. This can be accomplished by generating a database of participants and by removing dates of birth and dates of visit.

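### Section 3.11 sizes one 3-month contrast at alpha 0.01, but section 3.16 tests it in an unfixed Tukey-Kramer family at 0.05, so its power runs from about 56% to 86% by reading

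*Protocol*

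**What the plan says.** Protocol section 3.11 gives the basis of the sample size: "The minimum sample size (n=66) is based on the primary objective, lean mass in g at 3 mo of age". The difference is 400 g and the other inputs are "SD of 670 g, an allocation ratio of 1:1", 80% power and alpha 0.01. Enrolment is then raised to 74 per group for dropout and unusable scans. The section explains the strict level as an allowance for comparing the arms at several visits and for lean mass being more variable than expected.

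Section 3.16 describes the primary analysis: a mixed model with sex, dosage, time and the dosage-by-time interaction, and infant as a random effect. It is followed by "post-hoc testing as applicable (i.e. 2 treatment groups and 1 reference group over 4 time-points) using Tukey-Kramer correction and significant differences accepted at" the 5% level. The 0.01 level does not appear there, and the 3-month contrast between the randomised arms is not singled out.

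The reference infants are not randomised. Section 2 places them outside the trial, and section 3.5 selects them on 25(OH)D above 50 nmol/L and on maternal weight criteria.

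**The concern.** A power statement holds only for the test that will be carried out. Section 3.11 calculates power for one two-group test at 0.01. Section 3.16 describes a multiplicity-adjusted family at 0.05 that includes a third, non-randomised group and, on its face, every visit. Tukey-Kramer protects all pairs in its family, so each irrelevant cell (baseline, reference infants, pairs across visits) raises the bar for the one contrast that answers the trial's question.

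Two things are at stake. A true 400 g effect may have well under the planned 80% chance of being declared. And because the family is not fixed, the adjusted p value for the same 3-month difference depends on a choice that could be made after the data are seen.

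**Working it through.** **Inputs (Protocol section 3.11).** Difference 400 g; SD 670 g; 1:1 allocation; alpha 0.01; power 80%; 66 evaluable, 74 enrolled per group. Two inferences are needed. The 66 is per group, because it leads to 74 per group. The test is two-sided, because a one-sided 0.01 would need only 57.

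**The plan's own figure.** n per group = 2 × [(2.576 + 0.842) × 670/400]² = 65.5, so 66. Power at 66 is 80.3% by the normal formula and 79.1% by the noncentral t. Inflation: 66/0.90 = 73.3, so 74. The sizing reproduces.

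**Standard error of the 3-month contrast.** 670 × √(2/66) = 116.6 g, so the standardised difference is 400/116.6 = 3.43. With 74 per arm it is 670 × √(2/74) = 110.2 g, giving 3.63.

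**Power under each reading of section 3.16.** The Tukey critical value is q(0.95; k, ∞)/√2 for k means, and power = Φ(standardised difference − critical value). For k = 12, q = 4.622, so the critical value is 4.622/1.414 = 3.268. Power at 66 is Φ(3.430 − 3.268) = 56.4%, and at 74 it is Φ(3.631 − 3.268) = 64.2%.

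| Test of the 3-month contrast | Critical value | Two-sided level per contrast | Power, 66 per arm |
|---|---|---|---|
| Single contrast, 0.01 (section 3.11) | 2.576 | 0.010 | 80% |
| Tukey, 3 groups × 4 visits (12 means, 66 pairs) | 3.268 | 0.0011 | 56% |
| Tukey, 2 arms × 4 visits (8 means) | 3.031 | 0.0024 | 65% |
| Tukey, 3 groups within one visit | 2.344 | 0.019 | 86% |
| Bonferroni, 4 two-arm visit contrasts | 2.498 | 0.0125 | 82% |
| Single contrast, unadjusted 0.05 | 1.960 | 0.050 | 93% |

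With finite degrees of freedom the 12-mean figure is 55 to 56%.

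**What the 0.01 allowance buys.** 0.05/0.01 = 5 Bonferroni contrasts. It is also close to the per-contrast level of a four-mean Tukey family (0.0102). A 66-pair family needs about 0.0011.

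**Sample size if the 12-mean family is meant.** 2 × [(3.268 + 0.842) × 670/400]² = 94.8, so about 95 evaluable per group.

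**The case against.** The strongest reply is that section 3.16 limits the post-hoc tests to those that apply and never says that all 66 pairs form one family. If Tukey-Kramer is used across the three groups at each visit, power is 86%, above the target. Section 3.11 also budgeted for multiplicity, so its 0.01 can be read as a planning allowance for an adjusted 0.05 rather than as a rival level. And 66 is the minimum. Section 3.14 reports under 4% earlier loss at 3 months; about 71 per arm (74 × 0.96) would give about 61% even with 12 means. A wide Tukey family is also conservative: it costs power and does not raise the false-positive rate.

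Most of this stands. It means that 56% cannot be presented as the trial's power. It does not remove the mismatch: the allowance covers about five contrasts, section 3.16 does not mention it, and the bracket that defines the comparisons lists all three groups and all four visits. Nor is this only detail for a statistical analysis plan, since the protocol itself names the method, groups, visits and level, and they differ from those used for sizing.

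Three stronger inferences are tempting but not supported:

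- **A significant dosage-by-time interaction could come from the reference group alone.** With three groups and four visits that test has (3 − 1) × (4 − 1) = 6 degrees of freedom, so this is possible in principle. But section 3.16 does not make the interaction the decision rule, and the documents give no visit-specific SDs or correlations from which to quantify it.
- **The 3-year analysis lowers power further.** Section 3.17 on frequency says "For the primary outcome, one analysis will be conducted on blinded groups after all infants have completed 12 mo of study", with a second analysis at 3 years. It does not say that the Tukey family grows or that the 3-month contrast is retested.
- **The primary visit is contradictory.** Section 3.8 has "Primary outcome: lean mass during the trial; with follow-up thereafter to 3 y", which is looser than section 3.11. The objective in section 2, however, names 3 months with persistence to 3 years, which agrees with the sizing.

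**Conclusion.** The concern holds as a mismatch between sizing and analysis. The 80% in section 3.11 belongs to a single two-arm contrast at two-sided 0.01. Section 3.16 does not specify that test, and it leaves open the family that would replace it. Read literally, power for 400 g is about 56% at 66 per arm (64% at 74). Across the Tukey readings it runs from about 56% to 86% at 66 per arm. A reader might infer that the trial simply has 56% power; the open wording of section 3.16 does not support that.

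The figures assume a normal approximation, an SD of 670 g for the 3-month contrast, and the usual studentized-range critical value with cell means treated as independent and of equal variance. Within-infant correlation does not alter the simple between-arm contrast at 3 months, but it makes the Tukey critical value approximate.

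**What to change.** In section 3.16, name the randomised 1000 versus 400 IU/d contrast in lean mass at 3 months as the primary test, outside any Tukey-Kramer family, at the two-sided 0.01 used in section 3.11. That restores 80% power at 66 per arm (85% at 74). The two-arm contrasts at other visits can use the same allowance: section 3.7 lists five post-baseline visits (3, 6 and 12 months, 2 and 3 years), and 5 × 0.01 = 0.05. Put the reference group in a separate, secondary comparison, where Tukey-Kramer can stay.

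If the 12-mean family is intended, say so and restate the power in section 3.11 as about 56% (64% with all 74), or size for about 95 evaluable per group.

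The main option changes wording only and needs no extra infants. Its cost is that comparisons with the reference group become secondary. Testing the 3-month contrast at 0.05, or testing later visits in a fixed order, would also be coherent, but these are choices for the sponsor and are not needed to close the gap.

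### Section 3.16 wrongly says the mixed model needs no equal-variance assumption; if lean-mass spread grows with age and this is left unmodelled, visit-specific standard errors will be wrong

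*Protocol*

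**What the plan says.** Protocol section 3.16 analyses the primary outcome by mixed model ANOVA. The fixed effects are sex, dosage, time and the dosage-by-time interaction, "and random effects (e.g. infant ID.) with post-hoc testing as applicable". The post-hoc comparisons span "2 treatment groups and 1 reference group over 4 time-points", with "Tukey-Kramer correction and significant differences accepted at" p < 0.05. The section then states: "The mixed model ANOVA does not require that data be parametric nor of homogeneous variance". Normality tests follow, with data "where necessary transformed (e.g. log value etc.) to meet the assumptions of the post-hoc tests". It names no residual covariance structure. Primary results are to be given as means with 95% confidence intervals.

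Section 3.11 sizes the trial on "lean mass in g at 3 mo of age and an effect size of 9% (400 g), SD of 670 g", with "an allocation ratio of 1:1, power of 80 and alpha of 0.01". No SD is given for any other visit.

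**The concern.** The sentence is a positive statement about the primary analysis, and it is wrong. A standard linear mixed model assumes normal random effects and residuals. It also assumes one residual variance unless heterogeneity is specified. An analyst who takes the sentence at its word has no reason to specify it.

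Equal variance is doubtful here. Section 3.11 reports a gain of 670 g in lean mass between 1 and 3 months in the preliminary group, the visits run from 1 week to 12 months, and spread usually grows with size. Section 3.5 restricts the reference group by maternal BMI and pregnancy weight gain but does not restrict the trial arms by BMI, so variance may also differ by group.

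A random infant intercept with one residual variance gives the treatment difference the same standard error at every visit, based on the average variance. At stake are the 12-month tests and intervals, which bear on the sustained-benefit half of the primary objective, and power at 3 months, on which the trial is sized.

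**Working it through.** **1. The plan's own figure.** Per group, n = 2(2.576 + 0.842)² × 670² / 400² = 65.5, so 66, as stated (two-sided alpha 0.01, power 80%). For losses, 66 / 0.90 / 0.99 = 74.1, matching the stated 74. The sizing reproduces. It also implies a 3-month mean of 400 / 0.09 = 4,444 g and a coefficient of variation of 670 / 4,444 = 15%.

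**2. Formulas.** Take balanced data, n = 66 per arm, an infant random intercept and one residual variance. Let V be the mean of the four visit variances and S = √V.

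- Model standard error at every visit: S√(2/66). True standard error at visit t: SD_t√(2/66).
- Actual type I error at visit t for a nominal 0.05 test: 2[1 − Φ(1.96 S / SD_t)]. Coverage of the 95% interval is one minus this.
- Power at 3 months, alpha 0.01: Φ(400 / (670√(2/66)) − 2.576 S / 670).
- For Tukey-Kramer over 8 cells (2 arms × 4 visits), replace 1.96 by about 3.04, a nominal per-comparison error of 0.0023.

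**3. One scenario in full.** Assumed SDs are 400/670/760/870 g at baseline, 3, 6 and 12 months; only the 670 is from the protocol.

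- V = (160,000 + 448,900 + 577,600 + 756,900) / 4 = 485,850, so S = 697 g.
- Model standard error is 697 × 0.1741 = 121 g at every visit. True values are 70 g at baseline, 117 g at 3 months and 151 g at 12 months.
- 12-month type I error: 1.96 × 697 / 870 = 1.570, giving 0.116.
- 3-month power: Φ(3.430 − 2.680) = 0.773, against 0.803 with the correct SD.

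**4. Range of assumptions.**

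| SDs at 0/3/6/12 mo (g) | S (g) | Type I, 3 mo | Type I, 12 mo | Coverage, 12 mo | Power, 3 mo, alpha 0.01 | Tukey-Kramer per comparison, 12 mo |
|---|---|---|---|---|---|---|
| 670 throughout | 670 | 0.050 | 0.050 | 95% | 0.80 | 0.0023 |
| 500/670/720/780 | 676 | 0.048 | 0.090 | 91% | 0.80 | 0.008 |
| 400/670/760/870 | 697 | 0.041 | 0.116 | 88% | 0.77 | 0.015 |
| 452/670/844/1,055 | 787 | 0.021 | 0.144 | 86% | 0.66 | 0.023 |
| 350/670/850/1,100 | 791 | 0.021 | 0.159 | 84% | 0.65 | 0.029 |

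The fourth row holds the coefficient of variation at 15% with assumed means of 3,000/4,444/5,600/7,000 g. Type I and coverage are for unadjusted 0.05 contrasts. Unadjusted 12-month error reaches 0.10 when the 12-month SD is 1.96 / 1.645 = 1.19 times S. With Tukey-Kramer over 12 cells, reference group included, nominal 0.0010 becomes about 0.005 to 0.018.

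**5. Simulation.** With 8,000 trials per row, 66 per arm, serial correlation 0.7 and Satterthwaite degrees of freedom, 12-month type I error was 0.051, 0.081, 0.113, 0.141 and 0.160, in line with the formula. A separate variance at each visit gave 0.044 to 0.053.

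**6. Normality.** With equal variances and data of skewness 1.4, type I error at 66 per arm was 0.047, so non-normality alone does little.

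**The case against.** The strongest reply is that the faulty model is not actually specified. Infant ID is offered as an example of a random effect, no residual covariance is named, and a statistical analysis plan that is not shown may set one. That stands: the missing covariance structure is not itself a finding, and a reader who infers that the protocol commits to a single random intercept goes further than the text. It does not rescue the sentence, which says the assumption is absent.

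A reader might also infer that 12-month type I error roughly doubles as a matter of fact. The documents do not support that. They give one SD, and the multiple runs from 1.0 to about 3.2 with the SDs assumed. It also refers to an unadjusted contrast, whereas the plan uses Tukey-Kramer, under which per-comparison error stays below 0.05 in absolute terms, though several times its nominal value. The correction does not mend an unadjusted 95% interval built on the same standard error.

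Further points stand in the plan's favour. The 3-month comparison that sizes the trial is not inflated; the risk there is lost power, and at alpha 0.05 that is modest (0.93 falling to between 0.87 and 0.93). Transformation is confined to "transformed (e.g. log value etc.) to meet the assumptions of the post-hoc tests", so it does not flatly contradict the earlier sentence. A log transform would also largely remove a constant-coefficient-of-variation pattern. It would, however, replace the gram difference with a ratio. Whether one would be needed is unknown.

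**Conclusion.** The sentence is wrong as written and should go. Its consequence is conditional: it needs an SD that grows with age and a model with one residual variance. If both hold, the 12-month standard error is too small, and those at baseline and usually at 3 months are too large. The ranges in the table then apply; with a constant SD there is no harm. Every SD except 670 g at 3 months is an assumption, and the formulas assume complete, balanced data.

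The documents do not show that the trial's error rate is doubled, that the 3-month test is anti-conservative, or that the claim about normality matters materially at this sample size. The point concerns unequal variance, with a secondary caution about the scale of the primary estimate.

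**What to change.** Delete the sentence and replace it with a short specification:

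- Fit the repeated-measures model with an unstructured covariance across visits, with heterogeneous variances by visit as the fallback, using REML and Kenward-Roger degrees of freedom.
- If the reference group is in the model, give it its own covariance.
- Check model residuals rather than raw data.
- Report the primary treatment difference in grams, matching the 400 g on which the trial is sized, with any log-scale analysis as a sensitivity analysis.

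The cost is one paragraph, a covariance statement in SAS and a few extra parameters: four visits have 10 unstructured terms against 2 for a random intercept with one residual variance, which is small for 148 infants. No design change or extra recruitment is needed.
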